## 2. Methods and design

### 2.1. Participants

We aim to recruit 640 adult community members (18–35 years old, 50% female) through advertising on social media. The sample size was based on detecting significant differences among the groups (i.e., between SPs with MT vs. SPs with RT), assuming a moderate effect (Khoury et al., 2013a,^2015^), a power of 0.8 and an alpha of 0.05 (Cohen, 1977) and the expectation 15 to 20% attrition rate. We will exclude participants who: (1) have a regular meditation practice; (2) have already participated in a formal mindfulness training (such as MBSR or a meditation retreat); or (3) had a social support skills training (e.g., counselors, psychologists, social workers, or other medical personnel).

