#### 2.2.2. Mindfulness training (MT)

In the absence of a validated protocol for interpersonal mindfulness in a general context, that is, outside parenting (Kabat-Zinn and Kabat-Zinn, 1997), couple (Carson et al., 2004), or counseling (Cohen and Miller, 2009), MBSR remains the most used and validated protocol for the general population (Khoury et al., 2015). MBSR is an 8-week, 2.5 h weekly session program that comprises different types of meditations (sitting, walking, eating) in addition to yoga, psychoeducation, group discussion, a half-day meditation retreat, and at home practices (40 to 45 min 6 days weekly). Therefore, MBSR requires participants to commit to 2.5 to 3 h each week and 45 min of mindfulness practice each day for 8 weeks. This can impact adherence to the program. In fact, adherence to standard MBSR is approximately 85% among highly motivated participants, whereas among a student population, the adherence rate falls to 70% (Williams et al., 2001). Taking that into consideration, we will implement a shortened version of MBSR, called MBSR-ld (light). In MBSR-ld, the duration of weekly meetings is reduced to 1 h, the daily practice is also reduced to 20 min (Klatt et al., 2009). Studies showed significant improvement in mindfulness disposition following MBSR-ld (Bergen-Cico et al., 2013), comparable effects of MBSR-ld to the original protocol (Klatt et al., 2009), and lack of support of the significant effects of the number of in-class hours on MBSR outcomes (Carmody and Baer, 2009). Similarly, in a recent RCT, low-dose mindfulness-based intervention led to significant increase in trait mindfulness, self-efficacy, body awareness, and reappraisal (Karing and Beelmann, 2021). Each group will include 6 to 8 participants. Sessions will be facilitated by two Doctoral trainees who received formal MBSR training. To ensure the quality of the delivery of the program the trainees will be supervised by a registered clinical psychologist, certified in MBSR.

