#### 2.5.2. Experiment–Part II; mindfulness/relaxation training

SPs (total of 160) will be asked to complete measures of mindfulness, perceived stress, emotion regulation, empathy, compassion for others, active listening, perspective taking and interpersonal mindfulness. Then, they will be randomly and equally divided into two groups using a computer algorithm to ensure randomization and concealment. Half of the SPs (80) will receive the MT (MBSR-ld) and the other half will receive the RT. Participants in both groups will be asked to complete the daily logs during the 8 weeks. After the training, the same measures will be administered to the SPs.

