### 2.6. Timeline

The recruitment of participants will be divided into four cohorts (one cohort per year of 160, 40 SPs, and 120 SRs). The four parts of the experiment (i.e., Part-I, Part-II, Part-III, and Part-IV), will be repeated for each of the four cohorts. During each year (four in total), 40 SPs will be receiving training [MT(20), RT(20)]. The SPs receiving MBSR or RT will be divided into groups of 6 to 8 participants, and, a total of six groups will be conducted each year. We will conduct two groups (one MBSR, one RT) simultaneously during the fall, winter, and summer academic semesters of each year.

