## 3. Data analyses strategies

To ensure data reliability, self-reported data will be inspected for normality and skewness and outliers will be eliminated. Interrater reliability for the behavior observation data will be computed. An interrater coefficient of 0.95 or above is expected.

To test H1.1, H2.1, and H3.1, we will perform a mixed (2 groups × 3 time-points) multivariate analysis of covariance (MANCOVA) controlling for social desirability (and for Fears of Compassion from Others for H3.1). MANOVA/MANCOVA allow to reduce Type-I errors (i.e., rejecting the null-hypothesis when it is true, correcting therefore for multiple comparisons) when testing changes in multiple dependent variables. To test H1.2, we will use a regression analysis. To test H2.2 and H3.2, we will use a path analysis. To test associations and meditation/moderation at baseline (Hbase), we will use correlations and PROCESS macro with 5,000 bootstrapped/bias-corrected confidence intervals (Hayes, 2018). Structural Equation Modeling (Klem, 2000) may be used as well if the power is sufficient.

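### Training is delivered in 24 small groups, but the sample size and the MANCOVA treat support providers as independent; if outcomes correlate within group, type I error rises and the sample size leaves no margin

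*Protocol article*

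**What the plan says.** Protocol article, section 2.1 (Participants): "The sample size was based on detecting significant differences among the groups (i.e., between SPs with MT vs. SPs with RT", "assuming a moderate effect", with "a power of 0.8 and an alpha of 0.05" and "the expectation 15 to 20% attrition rate". No ICC or design effect is mentioned.

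Section 2.5.2: "Half of the SPs (80) will receive the MT (MBSR-ld) and the other half will receive the RT".

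Section 2.2.2, on mindfulness training: "Each group will include 6 to 8 participants". Section 2.2.3 describes relaxation training as similar in structure and duration, with group discussion. Section 2.6 says the SPs "will be divided into groups of 6 to 8 participants, and, a total of six groups will be conducted each year" for four years, with one mindfulness and one relaxation group running in parallel each semester.

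Section 3, for H1.1, H2.1 and H3.1: "we will perform a mixed (2 groups × 3 time-points) multivariate analysis of covariance (MANCOVA) controlling for social desirability", with Fears of Compassion from Others added as a covariate for H3.1. No training-group, facilitator or cohort term appears. The only dependence that section 3 addresses is between the two members of an SP-SR dyad, through the Actor-Partner Interdependence Model. The Monte Carlo power statements in sections 2.3 and 3 do not mention training groups, and neither do the limitations in section 4.

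**The concern.** People who train together for eight weeks share peers, group discussion and possibly facilitators. The SP outcomes include empathy, listening, stress and emotion regulation, so some correlation within a training group is plausible. Training groups are nested within arm, so variance between groups enters the arm contrast directly. A model that takes 160 SPs as 160 independent units leaves that variance out of the standard error.

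Two separate things are at stake. Ignoring the groups makes false positives more frequent than the nominal 5%. Modelling them restores the error rate, but at lower power than section 2.1 states. Dividing alpha for post hoc tests, as section 3 provides, does not help if each p-value is already too small.

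**Working it through.** **Inputs.**
- From the document: 80 SPs per arm (2.5.2); power 0.8, alpha 0.05 and attrition of 15 to 20% (2.1); 20 SPs per arm per year, six groups per year, four years (2.6).
- Assumed: d = 0.5 for a moderate effect, a two-sided test, and a group-specific ICC of 0.02 / 0.05 / 0.10. The calculation is for a single outcome at one time point.

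**Groups.** 6 × 4 = 24 groups, 12 per arm. Mean size at entry is 20/3 = 6.67. With 20% loss, 80 × 0.8 = 64 completers per arm, or 64/12 = 5.33 per group. With 15% loss, 68 completers, or 5.67 per group.

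**The plan's own figure.** A two-sample t test with d = 0.5, two-sided alpha 0.05 and power 0.80 needs 63.8, so 64 per arm; 64/0.8 = 80, the planned number. The normal approximation gives 63, and 63/0.8 rounds up to 79. A one-sided test needs only 50 before attrition and does not lead to 80. The match supports the two assumptions, and it means the planned number is the figure for independent SPs.

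**Design effect.** DE = 1 + (m − 1) × ICC. With m = 5.33 this is 1.09 / 1.22 / 1.43, so 64 completers are worth 58.9 / 52.6 / 44.7.

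**If the groups are ignored.** The standard error is understated by 1 − 1/√DE = 4% / 9% / 16%. Type I error is approximately 2 × [1 − Φ(1.96/√DE)] = 6.0% / 7.6% / 10.2%. A simulation of 40,000 trials gave 7.6% and 10.5% at ICC 0.05 and 0.10.

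**If the groups are modelled.** The noncentrality is d × √(n/(2 × DE)). At ICC 0.05 this is 0.5 × √(64/2.433) = 2.56. Group-level degrees of freedom are 24 − 2 = 22.

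| Completers per arm | ICC | Power, design effect only | Power, 22 df |
|---|---|---|---|
| 64 (20% attrition) | 0 | 0.80 | 0.77 |
| 64 | 0.02 | 0.77 | 0.74 |
| 64 | 0.05 | 0.72 | 0.69 |
| 64 | 0.10 | 0.65 | 0.62 |
| 68 (15% attrition) | 0.02 | 0.79 | 0.76 |
| 68 | 0.05 | 0.74 | 0.71 |
| 68 | 0.10 | 0.67 | 0.63 |

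Simulated power of a t test on group means with 64 completers per arm was 0.77 / 0.69 / 0.61 at ICC 0 / 0.05 / 0.10, in line with the last column.

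**The case against.** **The ICC is not in the document.** This stands. A reader might infer that the standard errors are certainly wrong and that 0.80 power is certainly missed. The document does not support that. At ICC 0 the standard errors are right. At ICC 0.01 with 15% attrition, design-effect power is still about 0.81.

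**Semester is shared by both arms.** This stands. A reader might count the common semester as a source of inflated error. Because section 2.6 runs one group of each arm in parallel, a pure semester effect cancels from the arm difference. If an ICC of 0.05 were all semester, simulated type I error is between 4% and 5%; if half semester and half group, about 6%. Facilitators are also uncertain as a source: if one pair leads every group in an arm, they add no variance between groups within that arm.

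**Part of the power loss is not clustering.** This stands. With 64 completers and ICC 0, moving to 22 df alone takes power from 0.80 to 0.77, which is why the table has both columns.

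**Baseline adjustment could recover power.** This stands in part. With an assumed baseline correlation of 0.5, design-effect power is about 0.84 at ICC 0.05 and 0.78 at ICC 0.10. Section 2.1 claims no such gain, and the adjustment would not by itself correct the standard errors.

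**One ICC range does not fit every hypothesis.** This stands. Support receivers never attend training, and a different one meets the SP at each time point, so a group effect reaches their ratings, affect and state mindfulness only through the SP.

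**Missing rows.** A reader might add that the MANCOVA discards every SP with an incomplete record. The article does not say how missing data are handled, and that may be set out elsewhere, so it forms no part of this point.

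**Conclusion.** The point holds conditionally. Section 3 names an analysis that treats SPs as independent, section 2.1 sizes the trial the same way, and the dyadic model covers a different kind of dependence. With a group-specific ICC of 0.02 / 0.05 / 0.10, the named analysis has a type I error of about 6% / 8% / 10%. An analysis that respects the groups has power of 0.62 to 0.74 on 22 df at 20% attrition, or 0.63 to 0.76 at 15%, before any baseline gain. These results rest on the assumed ICC range, d = 0.5 and a two-sided test. They apply most directly to H1.1; for support-receiver outcomes in H2.1 and H3.1 the effect may be smaller. The harm becomes material from an ICC of roughly 0.02 to 0.05 upward.

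**What to change.** Test the arm comparisons in H1.1, H2.1 and H3.1 with linear mixed models in place of the mixed MANCOVA:
- random intercepts for training group (24 levels) and for SP;
- the baseline value as a covariate or as one of the time points;
- the covariates already named in section 3;
- Kenward-Roger or Satterthwaite degrees of freedom.

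If a calendar effect is wanted, use the four cohorts as the fixed effect, which leaves about 22 − 3 = 19 group-level df. Using all 12 semesters would leave about 22 − 11 = 11.

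In section 2.1, state the effect size as a number and give power over a range of ICCs, with any assumed baseline correlation stated. Fix the model before outcome data are compared by arm.

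**Cost.** No change to conduct is needed, since group membership will be known from scheduling. The stated power becomes less favourable. Section 3 relies on the MANCOVA to limit type I error across outcomes; without it, multiplicity control must come from the division of alpha that section 3 already provides, which lowers power per outcome further.

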### 1.3. Main hypotheses

The following are the principal hypotheses of the study, and the numbering of the hypotheses is linked to the numbering of the objectives (e.g., H1.1 designates the hypothesis linked to the objective O1.1, Hbase designates the hypothesis at baseline, i.e., before randomization and the experimental procedure).

(H1.1) (a) Measures pertaining to S-ART will be significantly higher in SPs who receive MT compared to those who receive RT and thus, at post-training and at follow-up. The only measure that we hypothesize to be equally lower for both groups (at both time points) is stress. (b) Within-groups effects (i.e., among the three time points) will be significant for all the outcomes for the MT group, and only for stress for RT.

(H1.2) (a) The effects of MT on S-ART measures will be moderated by the adherence of the SPs to the practice at both time points (i.e., post-training and follow-up). (b) The effects of RT on stress will be moderated by the SPs’ adherence to practice.

(H2.1) (a) Objective and subjective measures pertaining to the quality of the SP-SR interactions will be significantly higher in dyads with a SP who received MT compared to dyads with a SP who received RT at both time points (i.e., post-training and follow-up). (b) Within-groups effects (across time) will be only significant for the dyads with an SP who received MT.

(H2.2) The effects of MT of the SPs on the quality of SP-SR interactions (measured subjectively and objectively) will be mediated by the increase on S-ART of the SPs at both times points (i.e., post-training and follow-up).

(H3.1) SRs who interacted with SPs who received MT training will show significantly (a) higher positive emotional states, lower negative emotional states and (b) higher mindfulness states following their interaction compared to those who interacted with SPs who received RT and thus, at both time points (i.e., post-training and follow-up). (c) Within-groups effects will be only significant for the SR who interacted with an SP with MT training.

(H3.2) The effects of MT of the SP on the emotional and mindfulness states of the SR will be mediated by the increase in the quality of the SP-SR interaction and moderated by SRs’ Fears of Compassion from Others (i.e., higher fears of compassion will reduce the mediation effects) at both time points (i.e., post-training and follow-up).

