(Hbase) (a) At baseline, the S-ART measures of the SPs will be associated with the quality of SP-SR interactions (as measured objectively and subjectively) and with the emotional and mindful state of the SR and (b) the association between the S-ART of the SPs and the emotional/mindful states of the SR will be mediated by the quality of SP-SR interactions and moderated by Fears of Compassion from Others.

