The effects of the training on the SP-SR interaction (O2.1/O2.2) will be assessed subjectively by the SRs using the Multidimensional Evaluation of Enacted Social Support (MEESS; Goldsmith et al., 2000), which includes three dimensions: *helpful*, *supportive*, and *sensitive* (Goldsmith and Fitch, 1997; Goldsmith et al., 2000; Goldsmith, 2016; Goldsmith and Griscom, 2017). While helpfulness focuses on providing assistance, or perspective (Dunkel-Schetter and Bennett, 1990; Goldsmith, 1992, 1994; Cutrona and Suhr, 1994), supportiveness refers to validation (non-judging or criticizing) (Winstead et al., 1992; Cutrona and Suhr, 1994) and sensitivity relates to the emotional support (Burleson, 1994; Burleson and Goldsmith, 1996). The scale is composed of 12 semantic items scaled on seven points and demonstrated high reliability and construct validity (Goldsmith et al., 2000). The MEESS was developed using student/community samples and has since been used in a variety of populations and situations (Goldsmith and Griscom, 2017), making it highly suitable for this study. To rate the quality of the dyadic interaction objectively, we will use the Behavioral Observational Measure of Dyadic Interactions (BOMDI; Cuperman and Ickes, 2009), which assesses verbal and non-verbal behaviors of the SP during their interaction with the SR. The BOMDI comprises seven verbal and nine non-verbal items. Verbal items include for example, the number of verbal acknowledgments displayed by the SP. Non-verbal items include for example, head nods, facial expressions, and eye contact. These measures assess the level of empathic listening and perspective taking of the SP during the interaction. Inter-rater reliability is high (Cuperman and Ickes, 2009). To ensure better reliability, two independent trained research assistants will code the dyadic interaction according to the BOMDI. Differences of two points or more between the raters will be discussed and if consensus is not reached, the primary investigator will be contacted.

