As suggested by IER and SBT, attentive, empathic, and caring interpersonal interactions can help the SR to better self-regulate and such a regulation process is economic (i.e., requires less cognitive and emotional resources), therefore automatically triggered without the conscious awareness of the individual on the receiving end (Eisenberger et al., 2007). This is even more true following a negative emotional state, such as following the negative mood induction. SBT suggests that this process allows the support receiver (SR) to return to a baseline, which in our experimental paradigm, is a return to an emotional/mindful state similar to that before the mood induction. Therefore, the effects of mindfulness training of the SP on the SR (O3.1/O3.2) will be assessed using the Positive and Negative Affect Schedule (PANAS; Watson et al., 1988), which comprises 20 items, 10 measuring PA (e.g., excited, internal consistency = 0.89), and 10 NA (e.g., upset, internal consistency = 0.85). The PANAS was designed to measure affect in various contexts such as at present, and in the past, and demonstrated high construct validity (Crawford and Henry, 2004). Thus, it can be used to measure fluctuations in emotions (Tran, 2013), making it highly suitable for the current study. In addition, state mindfulness of the SR will be measured using the Mindful Attention Awareness Scale-State (MAAS-State; Brown and Ryan, 2003), which includes only five items and can be used in a non-meditative context, making it suitable to measure fluctuations in mindfulness state in the current context. To control for the response of SRs to the social support received from the SPs, we will use the Fears of Compassion from Others (FOCO; Gilbert et al., 2011). Finally, to control for Social Desirability we will use Marlowe-Crowne Social Desirability Scale (SDS; Crowne and Marlowe, 1960) for the SP and SR. Measures will be completed either using a paper-based format or on a tablet depending upon the preference of the participants. See Table 1 for a summary of the sequence of administering the measures. To film and record the dyadic (SP-SR) interactions, a high-definition 360-degree camera (1080P HD 360°Camera) with a built-in recording system will be used. The experiment will take place at the first author’s lab at McGill University.

**TABLE 1 T1:** Sequence of administering the measures during the experiment.

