### 2.5. Experimental procedure

#### 2.5.1. Experiment–Part I; pre-training

A total of 160 (SP, SR1) dyads will be invited to the lab. Upon arriving to the lab, members of each dyad will meet separately with two different research assistants (RAs). After signing a consent form, providing basic socio-demographic data, and filling-in the SDS, the SR will be asked to complete the FOCO (Gilbert et al., 2011), PANAS (Watson et al., 1988), and the MAAS-State (Brown and Ryan, 2003). Afterward, the SR will receive the 15-min mood induction while the SP will wait in a separate room doing an activity of their choice (e.g., reading popular magazines). Then, the SR will be asked to complete the PANAS and MAAS-State for a second time (as a check of the induction). Afterward, the SP and SR will be introduced to each other, the SR will be asked to discuss with the SP the event (which was part of the induction), and the SP will be asked to provide support to the SR as best they can during a 15-min videotaped interaction. The interaction will occur face-to-face, will be recoded, and the video will be rated by two trained graduate students according to the BOMDI (Cuperman and Ickes, 2009). Both the SP and SR will also be blind to the objectives of the study. Following the interaction, the SR will be asked again to complete the PANAS, MAAS-State, and the MEESS (Goldsmith et al., 2000). At the end of this part of the experiment, the SR will be debriefed about the study and its objectives.

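### H2.1 is adjusted for social desirability only; adding the receiver's pre-interaction Fears of Compassion score, already collected, could sharpen the MT–RT contrast on the receiver-rated MEESS

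*Protocol article*

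**What the plan says.** Section 3 (Data analyses strategies) tests H1.1, H2.1 and H3.1 with a mixed MANCOVA of 2 groups by 3 time points, "controlling for social desirability (and for Fears of Compassion from Others for H3.1"). As an adjustment covariate, FOCO is thus attached to H3.1 and to no other MANCOVA. No reason is given for leaving it out of H2.1.

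H2.1 (section 1.3) states: "Objective and subjective measures pertaining to the quality of the SP-SR interactions will be significantly higher in dyads with a SP who received MT". Section 2.4 defines the two kinds of measure. The interaction "will be assessed subjectively by the SRs using the Multidimensional Evaluation of Enacted Social Support", whose dimensions are helpful, supportive and sensitive. The objective measure, the BOMDI, is coded from video by trained raters and "assesses verbal and non-verbal behaviors of the SP during their interaction with the SR".

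Section 2.4 gives the purpose of FOCO: "To control for the response of SRs to the social support received from the SPs, we will use the Fears of Compassion from Others". On timing, section 2.5.1 says that before the mood induction "the SR will be asked to complete the FOCO"; Table 1 lists FOCO as a control variable measured on the SR pre-induction. Sections 2.5.3 and 2.5.4 repeat the procedure with a new SR at post-training and at follow-up.

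FOCO has two further roles, both as a moderator. H3.2 names "Fears of Compassion from Others (i.e., higher fears of compassion will reduce the mediation effects"), and Hbase(b) has the association "mediated by the quality of SP-SR interactions and moderated by Fears of Compassion from Others".

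**The concern.** The MEESS asks the receiver how good the support was. FOCO measures how far that receiver fears or resists compassion from others. The article itself argues that this trait matters: section 1.1 says that interpersonal regulation requires the receiver to be open to support, and section 1.2.3 says that acceptance or fear of support influences how well it works. That reasoning applies to the receiver's rating of support at least as readily as to the receiver's mood afterwards.

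The design makes the point a little sharper. Each SP meets three different SRs, so differences between raters do not cancel when change is computed within an SP. They remain as residual noise in the group and group-by-time contrasts for the MEESS. FOCO is a recorded part of that rater variation, and the SP's training cannot have affected it. At stake is the width of the interval for the MT–RT contrast on the MEESS, within the hypothesis that links training to interaction quality.

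**Working it through.** **Inputs from the protocol article.** A moderate effect, power 0.8, alpha 0.05 and attrition of 15 to 20% (section 2.1); 80 SPs per training arm (section 2.5.2), hence 80 dyads per arm per visit (sections 2.3 and 3).

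**Assumptions.** Moderate means d = 0.5, in units of the MEESS residual SD after social desirability. The test is two-sided. ρ is the within-arm FOCO–MEESS correlation after social desirability. The article does not give it, so a range of 0.1 to 0.5 is shown. The calculation compares two arms at one visit; it is not the full 2 × 3 MANCOVA.

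**Step 1: the plan's own number.** n per arm = 2 × (1.96 + 0.84)² / 0.5² = 63 by the normal approximation, or 64 by the t-test. With 20% attrition, 64 / 0.80 = 80. The stated 80 per arm is reproduced, so the sample size is not in question.

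**Step 2: effect of adjustment.** Adding FOCO multiplies the residual variance by (1 − ρ²), so:

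- standard error ratio = √(1 − ρ²)
- effective sample gain = 1 / (1 − ρ²) − 1
- n per arm for 80% power = 63 (unrounded 62.8) × (1 − ρ²), rounded up
- power at 64 completers per arm = Φ( 0.5 / [√(1 − ρ²) × √(2/64)] − 1.96 )

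For ρ = 0.3: 1 − 0.09 = 0.91; √0.91 = 0.954; 1/0.91 − 1 = 9.9%; 0.5 / (0.954 × 0.1768) − 1.96 = 1.005; Φ(1.005) = 84.3%.

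| ρ | Residual variance | Fall in SE | Effective sample gain | n per arm for 80% power | Power at 64 per arm |
|---|---|---|---|---|---|
| 0 (no FOCO) | 1.00 | – | – | 63 | 80.7% |
| 0.1 | 0.99 | 0.5% | 1.0% | 63 | 81.1% |
| 0.2 | 0.96 | 2.0% | 4.2% | 61 | 82.3% |
| 0.3 | 0.91 | 4.6% | 9.9% | 58 | 84.3% |
| 0.4 | 0.84 | 8.3% | 19.0% | 53 | 87.0% |
| 0.5 | 0.75 | 13.4% | 33.3% | 48 | 90.4% |

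**Step 3: the same loss seen as chance imbalance.** With 80 SRs per arm at a visit, the 95% range for the arm difference in mean FOCO is ±1.96 × √(2/80) = ±0.31 SD. At ρ = 0.3 that could move the unadjusted MEESS contrast by about 0.3 × 0.31 = 0.09 SD. This is the variance of step 2 in another form, not an additional loss.

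**The case against.** **FOCO has other uses.** A reader might infer that FOCO is used for H3.1 and nowhere else. That is not so: it is the moderator in H3.2 and in Hbase(b). The point concerns only its role as an adjustment covariate in the MANCOVAs.

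**The sections need not contradict each other.** Section 2.4 introduces FOCO in the paragraph on effects on the SR (O3.1/O3.2), after the affect and state-mindfulness scales, not in the paragraph on the MEESS and BOMDI. Read there, the SR's response can mean the affective and mindfulness response, and its use in H3.1 follows that layout. This stands: a reader might infer an internal contradiction, but the text does not establish one. What remains is that the same rationale reaches the MEESS and no reason is given for stopping short of it.

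**No bias arises.** SRs are allocated to dyads by a randomising algorithm (section 2.3) and SPs are randomised to training (section 2.5.2). The unadjusted contrast is unbiased, and chance imbalance is already covered by the test's error rate. This stands in full.

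**The gain is unproven.** With no correlation given, it could be trivial: at ρ = 0.1 power moves from 80.7% to 81.1% and the required n does not change. Little gain is expected for the BOMDI, which codes SP behaviour. This also stands, and the conclusion has to be conditional.

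**Adjustment could break the joint test.** A standard MANCOVA uses one covariate set for all outcomes, so adjusting the MEESS alone would split the test that section 3 relies on to limit Type I error. That is a good argument against an outcome-specific covariate. It does not count against adding FOCO to the whole H2.1 model.

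**Conclusion.** The point holds as a cheap improvement. Section 3 fixes the H2.1 covariates and leaves out a pre-interaction measure of the rater that the trial collects anyway and that its own reasoning links to how support is received. The consequence is a possible loss of precision for the MT–RT contrast on the MEESS. It is negligible at a correlation of 0.1, worth about 10% more dyads at 0.3 and about 33% at 0.5. These figures rest on an assumed correlation, d = 0.5 and a single-visit approximation.

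The article does not support saying that precision is certainly lost, that the H2.1 result would be biased, or that the sample size is wrong.

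**What to change.** In section 3, extend the parenthesis so that Fears of Compassion from Others is a covariate for both H2.1 and H3.1. Enter the FOCO score of the SR seen at that visit as a visit-specific covariate, as H3.1 already requires because each SP meets three different SRs. Use one covariate set for the whole H2.1 model, so that the joint MANCOVA over the MEESS and BOMDI is preserved. If FOCO is deliberately kept out of H2.1, state the reason instead.

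No new data are needed. The cost is a few degrees of freedom: if the three visit scores enter separately, 3 against 160 − 2 = 158 error degrees of freedom with full follow-up, or 128 − 2 = 126 with 64 completers per arm. The BOMDI outcomes bear the same cost with little expected gain. The change should be made before outcome data are examined, so that the covariate is not chosen on the results.

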#### 2.5.3. Experiment–Part III; post-training

This part will take place after the end of the training and is similar to Part I, the only difference is that SR1 will be replaced by SR2 in the dyads. In addition, only the SR will complete the consent form and provide socio-demo/social desirability data, as SPs already did that in Part I.

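### H3.1 compares scores from a different receiver at each time point and leaves each receiver's own pre-interaction PANAS and MAAS-State out of the model: a valid test, but less efficient than the data allow

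*Protocol article*

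**What the plan says.** Each support provider (SP) meets a new support receiver (SR) at every part of the experiment. Section 2.3 forms three dyads per SP with different SRs. Section 2.5.3 describes Part III by saying that "the only difference is that SR1 will be replaced by SR2 in the dyads", and Section 2.5.4 does the same for SR3. Only the SP recurs.

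Within a session the SR completes the PANAS and MAAS-State three times: before the induction, after it, and after the interaction (Table 1). On the middle one, Section 2.5.1 says: "Then, the SR will be asked to complete the PANAS and MAAS-State for a second time (as a check of the induction").

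Objective O3.1 in the Introduction concerns changes in the SR's affective and mindfulness states. Section 2.4 describes the return to baseline, in this experiment, as "a return to an emotional/mindful state similar to that before the mood induction".

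Section 3 tests H1.1, H2.1 and H3.1 with a mixed MANCOVA of two groups by three time points, "controlling for social desirability (and for Fears of Compassion from Others for H3.1"). No earlier PANAS or MAAS-State score is listed. Table 1 nevertheless labels emotional experience as both a control and a dependent variable, and state mindfulness as dependent only.

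**The concern.** Two features of the H3.1 model cost precision.

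First, its arm × time term sets the mood of one person at Part III or IV against the mood of another person at Part I. In an ordinary repeated-measures design the baseline removes stable differences between people. Here the Part I score belongs to a stranger and shares only the SP with the later score. It is subtracted at full weight although it may carry little information.

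Second, the scores that do carry information about the receiver, namely that person's own state before and after the induction, are not in the stated model. Differences in ordinary mood and in response to the induction then stay in the error term. The stated covariates also do not match an objective framed as change, or Table 1's labelling of the PANAS as a control.

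At stake are the power of H3.1 and the match between its test and the recovery process that the theory describes.

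**Working it through.** **Inputs from the article.** Section 2.1 gives "a power of 0.8 and an alpha of 0.05", "assuming a moderate effect" and "the expectation 15 to 20% attrition rate", for the contrast "between SPs with MT vs. SPs with RT". Section 2.5.2 gives 80 SPs per arm.

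**Assumptions.** The article gives none of these.
- The test is two-sided.
- A moderate effect means d = 0.5.
- ρ, the correlation between the outcomes of two SRs who met the same SP, is 0 to 0.3, with 0.5 as an upper case.
- r, the correlation between one SR's own earlier and post-interaction score, is 0.3 to 0.7.

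**Step 1: reproduce the plan's figure.** A two-sample t-test at d = 0.5, two-sided alpha 0.05 and power 0.80 needs 63.8, so 64 per arm. With 20% attrition, 64 / 0.80 = 80 per arm. The stated 80 is therefore the size for one between-group comparison. The Monte Carlo result cannot be rerun, because its inputs are not printed.

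**Step 2: direct comparison at one part, no adjustment.** Power is 0.80 with 64 per arm and 0.88 with all 80.

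**Step 3: arm × time contrast, SR2 minus SR1.** In units of the outcome variance, the variance of the difference is 2(1 − ρ). The standardised effect is 0.5 / √[2(1 − ρ)].

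| ρ | Variance | Power, 64 per arm | Power, 80 per arm |
|---|---|---|---|
| 0 | 2.0 | 0.51 | 0.60 |
| 0.1 | 1.8 | 0.55 | 0.65 |
| 0.2 | 1.6 | 0.60 | 0.70 |
| 0.3 | 1.4 | 0.66 | 0.76 |
| 0.5 | 1.0 | 0.80 | 0.88 |

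The 2-df omnibus arm × time test, with effects of 0, 0.5 and 0.5 at the three parts, gives much the same: 0.52 to 0.68 with 64 per arm for ρ from 0 to 0.3.

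**Step 4: use the Part I value as a covariate instead of subtracting it.** The residual variance is 1 − ρ², that is 1.0 to 0.91 for ρ from 0 to 0.3. Power with 64 per arm is 0.80 to 0.84.

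**Step 5: adjust a one-part comparison for the SR's own earlier score.** The residual variance is 1 − r². This applies to PANAS and MAAS-State only.

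| r | Residual variance | Power, 64 per arm |
|---|---|---|
| 0.3 | 0.91 | 0.84 |
| 0.5 | 0.75 | 0.90 |
| 0.6 | 0.64 | 0.94 |
| 0.7 | 0.51 | 0.98 |

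**The case against.** The strongest reply is that Section 3 does not say which MANCOVA term decides. Parts (a) and (b) of H3.1, and part (a) of H2.1, are worded as group differences at post-training and at follow-up, and Section 3 foresees follow-up ANOVAs or t-tests. If the direct comparison at each part is the test, step 2 applies and the planned power is met. This stands, and it makes the loss in step 3 conditional. Against it, Sections 2.3 and 3 describe 80 dyads per group as sufficient for changes between time points, so a change contrast is clearly in view. Section 3 ties that simulation to the additional actor-partner models, and nothing stated for those models brings in the SR's own earlier score.

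It can also be said that Section 3 never defines the SR dependent variable, so a within-session change score may be intended. That is possible. The named covariates and Table 1 would still need to be brought into agreement.

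A reader might infer four stronger things that the article does not support.
- **That the test is invalid.** The SP is the unit randomised to training and is seen three times, and SRs are allocated to SPs by computer algorithm. Differencing across receivers adds noise, not bias.
- **That own earlier scores are also omitted for H2.1.** None exist: the MEESS is completed only after the interaction, and the BOMDI is coded from it.
- **That the power loss extends to the BOMDI.** It rates the behaviour of the same SP on three occasions, so it is an ordinary repeated measure and the assumed ρ does not describe it.
- **That a MANCOVA cannot adjust for each receiver's Fears of Compassion score.** A row per SP can carry the three receivers' values as three covariates. The data layout is a detail that an article may leave out.

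**Conclusion.** The point holds for H3.1 as lost efficiency and a mismatch of wording. The stated covariates leave out the receiver's own earlier PANAS and MAAS-State, while the objective is framed as change and Table 1 lists the PANAS as a control.

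If arm × time decides, power with 64 completers per arm is roughly 0.51 to 0.66 rather than the intended 0.80. That range rests on d = 0.5 and an assumed ρ of 0 to 0.3, and the shortfall vanishes at ρ = 0.5. If the comparison at each part decides, there is no shortfall against the plan, and own-score adjustment is a gain, from 0.80 to between 0.84 and 0.98 for r of 0.3 to 0.7. The article supplies neither correlation.

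For H2.1, only the point about a changing receiver carries over, and only to the MEESS. Overall this is a free improvement to the analysis, not a must-fix.

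**What to change.** **PANAS and MAAS-State (H3.1).** Replace the 2 × 3 MANCOVA by a linear mixed model of the post-interaction score at Parts III and IV with:
- arm, part and their interaction;
- that receiver's own pre-interaction score or scores on the same scale (post-induction, and pre-induction as well if wanted);
- that receiver's own Fears of Compassion and social desirability scores;
- the SP's Part I dyad value on the same outcome;
- a random effect for SP.

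Name the arm difference at each part as the test.

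**MEESS (H2.1).** Use the same model without the own-score terms. The arm difference at each part, adjusted for the SP's Part I value, is again the test.

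**BOMDI (H2.1).** It can stay a repeated measure on the SP.

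**Table 1 and Section 3.** Make the two agree on whether emotional experience and state mindfulness before the interaction serve as control variables.

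**Cost.** Only the wording of the analysis changes. Every covariate is already scheduled for collection before the receiver's outcome is measured, so no participant, visit or questionnaire is added. The change should be fixed before the outcome data are analysed by arm.
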